### Study design

PANUSCO is an open label, controlled, prospective, randomized, multicentre phase IIIb trial with two parallel study arms (Figure 1). All Patients receive chemotherapy (a combination of 5-flourouracil (5-FU), folinic acid (FA) and oxaliplatin) at an outpatient's basis at the study sites. Additional, the patients in experimental group receive BSNC expanded with PN containing a total of 1150 kcal for each application. PN will be given by medical-experienced staff overnight at patients home. The control group receives solely BSNC consisting of nutritional advice. Every kind of enteral nutrition and oral supplementation is allowed for patients in both study arms.

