### Study objectives

Primary objective is the comparison of the treatment groups with respect to event-free survival (EFS). EFS is defined as the time from randomization till time to development of an event defined as either an impairment (change from baseline of at least ten points in EORTC QLQ-C30, functional domain total score) or withdrawal due to fulfilling the special defined stopping criteria for chemotherapy as well as PN and Best Supportive Nutritional Care (BSNC) in Arm A or BSNC alone in Arm B or death from any cause (whichever occurs first). Chemotherapy will be continued until individual stop-criteria (disease progression, unacceptable toxicity) are met. This is unaffected by the (dis-) continuation of NI in both study arms. NI in both arms will be stopped when two of the three following criteria are met:

1. weight loss > 2% within the last seven days or caloric intake ≤ 500 kcal expected within the next five days,

2. BIA (Bioimpedance Analysis) defined by phase angle and body cell mass (BCM) with a deterioration > 10% (in both parameters)

3. Prognostic Inflammatory and Nutritional Index (PINI) > 10 (only in subjects with no sign of acute inflammation).

This is unaffected by the (dis-) continuation of chemotherapy.

Secondary objectives are the comparison of the treatment groups with respect to tumour-cachexia, Objective Response Rate (ORR), Time to Progression (TTP), Progression Free Survival (PFS), Overall Survival (OS), Toxicity, time from randomization till time point when stopping criteria are met. Furthermore, the definition and evaluation of a scoring system identifying subject groups who will benefit from second line chemotherapy and/or PN.

Accompanying translational research is focussing mainly on molecular signalling as well as on inflammatory parameters. The available results will be correlated with the clinical parameters.

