### Randomisation and standardised treatment scheme

All patients enrolled will be identifiable throughout the study. The investigator will maintain a personal list of patient numbers and patient names to enable records to be found at a later date. Upon inclusion each patient receives a unique identification number. After the patient's eligibility for randomisation has been assessed he/she will be randomly assigned to one of the two treatment arms (1:1) and receives a unique randomization number. The randomisation will be done and documented centrally and send by fax. Stratification will be performed prior to randomization by Eastern Cooperative Oncology Group Performance Status (ECOG PS) (stratum 1: PS < 2, stratum 2: PS ≥ 2). The randomisation list will be kept in safe and confidential custody at the involved CRO. The method of randomisation and the block sizes themselves will not be disclosed to the study sites, the monitors or any person involved in the clinical trial conduct. This information will be kept with the randomisation list.

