### Treatment scheme

After implantation of a catheter patients will be treated as follows:

Both study arms receive a chemotherapy consisting of 2000 mg/m^2^/day 5-FU by IV (24 hours) 200 mg/m^2^/day FA IV (30 min) on day 1, 8, 15 and 22 together with 85 mg/m^2^/day oxaliplatin IV (2 hour) on day 8 and 22. Therapy will be interrupted between days 23 to 42. This cycle will be repeated until any stop-criterion for chemotherapy (disease progression or unacceptable toxicity) is met.

Furthermore, all patients receive nutritional consultation and recommendation by experienced nutritionist contemplated as BSNC.

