#### Secondary analyses

A sensitivity analysis will be performed on the primary variable to assess the impact of protocol deviations using the per protocol analysis set.

The hazard ratio and the related 95% confidence interval (CI) for the experimental arm relative to control arm will be estimated by proportional hazard regression with treatment, centre and performance status as covariates.

OS, PFS, and TTP will be analyzed in the same manner as in the primary efficacy endpoint. Estimates of the ORR and 95% CI will be calculated and will be compared between treatment groups using the Cochran-Mantel-Haenszel (CMH) test adjusting by the stratification variables used in the stratified log rank test. For subjects with incomplete follow-up, time to last follow-up date will be used as the censoring time in the analysis of time-to-event data.

Descriptive statistics will be provided for the tumour-cachexia parameters. QoL scales, subscales and single item scores will be summarized by the mean and median for each arm and plotted by time. QoL data will be analysed using ANCOVA techniques. A logistic regression analysis will be carried out to identify relevant prognostic factors.

Incidence rates and 95% CI of Adverse Events (AEs) will be summarized. Subject disposition will be tabulated. Baseline characteristics, concomitant medications, vital signs and PS will be tabulated. Study drug administration and reasons for the deviations from the planned therapy will be tabulated. Summary tables will be prepared to examine the distribution of laboratory measures over time.

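### The scoring-system objective claims to identify who benefits from second-line chemotherapy, which a trial giving every patient the same chemotherapy cannot show

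*Protocol article*

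**What the plan says.** The last secondary objective in the Study objectives section of the protocol article is the "definition and evaluation of a scoring system identifying subject groups who will benefit from second line chemotherapy and/or PN".

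On who receives what:
- Study design: "All Patients receive chemotherapy", and the regimen is the same 5-FU, folinic acid and oxaliplatin combination throughout. On the nutritional side, "The control group receives solely BSNC consisting of nutritional advice", while the experimental arm has PN added.
- Treatment scheme: "Both study arms receive a chemotherapy consisting of" introduces one drug list that serves both arms.
- Randomisation: allocation is 1:1 between these two arms, so PN is the only randomised difference.

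On analysis, the Secondary analyses section names two regressions that bear on patient factors:
- "A logistic regression analysis will be carried out to identify relevant prognostic factors", with neither the outcome nor the scoring system mentioned.
- A "proportional hazard regression with treatment, centre and performance status as covariates", which gives one overall hazard ratio for PN.

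The Sample size estimation section leaves the details of the analysis to a statistical analysis plan, which is not available here.

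**The concern.** To say that a group benefits from a treatment is to compare how its members fare with the treatment and without it. For chemotherapy this trial has only the first half of that comparison. A score developed here can separate patients who do well on the study chemotherapy from those who do badly, but it cannot say whether the first group did well because of the chemotherapy.

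PN differs, because patients with and without it are randomised. Even so, a factor associated with a good outcome in both arms is prognostic and says nothing about who gains from PN. That question needs the PN effect to be compared between levels of the factor. If the named prognostic-factor regression were the basis of the score, a statement about benefit would not follow from it.

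At stake is what the trial may conclude on this secondary objective. As worded, the objective invites a conclusion about chemotherapy that the data cannot carry.

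**Working it through.** **1. Chemotherapy half.** No arithmetic applies. Setting the sections side by side:
- The objective requires a contrast between chemotherapy and no chemotherapy, within groups of patients.
- Study design and Treatment scheme assign the same chemotherapy to both arms, so no patients are assigned to go without it.
- The contrast is therefore not estimable overall or in any subgroup, and a larger sample would not help.
- Differences in how long patients stay on chemotherapy do not replace the missing group. Treatment stops at progression or unacceptable toxicity, so its duration is partly a result of the outcome.

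**2. The plan's own event number.** Inputs from Sample size estimation: 4-month EFS of 60% and 40%, two-sided level 0.05, power 0.80, 1:1 allocation.
- HR = ln(0.6)/ln(0.4) = 0.5575.
- Schoenfeld: 4 × (1.960 + 0.842)² / (ln 0.5575)² = 91.96.
- Multiplying by about 1.008, the usual inflation for a two-stage O'Brien-Fleming design (my input), gives 92.7, rounded to 93.

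The stated 93 events reproduce, so nothing is wrong there.

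**3. PN half: what 93 events can show about who benefits.** Assume a binary baseline factor with prevalence q, two-sided level 0.05, and r as the ratio of the PN hazard ratios between the factor's two levels.
- SE of ln r = √[4/(93 × q × (1 − q))]. For q = 0.5 this is √(16/93) = 0.415.
- Power at r = 2 is Φ(ln 2/0.415 − 1.960) = Φ(−0.29), about 39%. It is 33% for q = 0.3 and 27% for q = 0.2.
- Ratio detectable with 80% power at q = 0.5: exp[(1.960 + 0.842) × 0.415] = 3.2.
- Events for 80% power at r = 2 and q = 0.5: 16 × (1.960 + 0.842)² / (ln 2)² = 261.4, rounded up to 262.
- For an interaction as large as the planned main effect (r = 0.557), power is 29%, 25% and 20% for q = 0.5, 0.3 and 0.2.

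**4. Prognostic versus predictive, in the named type of model.** An illustrative simulation used assumed inputs: 2,000 trials of 120 patients, a 50:50 factor that halves the hazard equally in both arms, and being event-free at 4 months as the outcome. The main-effects logistic regression flagged the factor in 72% of trials. The PN-by-factor term was significant in 5.6%, close to the nominal 5%. A prognostic model thus readily selects a factor that does not change the relative effect of PN. That is no fault in the model, which simply answers a different question.

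**The case against.** The strongest reply is that most of the worry rests on things the article does not say. The logistic regression is not tied to the scoring system: the sentence follows the quality-of-life analyses and names no outcome, and a prognostic-factor analysis is legitimate in its own right. PN is randomised, and analysis details are left to a statistical analysis plan that could well specify interactions. The objective is also the last secondary one, and nothing says that the score will guide care.

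Much of this stands. A reader might infer that the trial will report prognosis as treatment benefit. The article does not support that, since it never says how the score will be built. The absence of an interaction term from a condensed article is likewise no finding. Nor can one infer that the score will be judged on its development data without correction, because the article does not describe how it will be evaluated.

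The reply does not reach the chemotherapy half. The article itself fixes the design, and no analysis plan can supply patients without chemotherapy. The wording 'and/or' does not help, because chemotherapy benefit remains a named target. If benefit is read charitably as doing well on chemotherapy, it means prognosis under treatment, and the objective should say so.

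**Conclusion.** The point holds for chemotherapy as a contradiction between the objective and the design. The trial cannot identify who benefits from second-line chemotherapy, and this rests on no numerical assumption.

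For PN the point is conditional. If the prognostic-factor regression were used to build the score, it could not by itself support a claim of benefit. A PN-by-factor analysis could address the question, but only as exploration: about 39% power for a ratio of hazard ratios of 2, given 93 events and a 50:50 factor, and less with a more uneven split.

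Severity is minor. The objective is secondary, and the primary EFS comparison, sample size and interim analysis are untouched.

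**What to change.** - In Study objectives, delete the reference to second-line chemotherapy from the scoring-system objective, or restate that part as *prognosis under the study chemotherapy*.
- Keep the logistic regression in Secondary analyses, described as a prognostic analysis.
- State that any conclusion about who benefits from PN will rest only on PN-by-baseline-factor interactions for EFS, and label it exploratory because of the limited power.

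This costs one reworded clause and a sentence or two on analysis, with no additional patients or data. The downside is a weaker, exploratory claim for the score.

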### Randomisation and standardised treatment scheme

All patients enrolled will be identifiable throughout the study. The investigator will maintain a personal list of patient numbers and patient names to enable records to be found at a later date. Upon inclusion each patient receives a unique identification number. After the patient's eligibility for randomisation has been assessed he/she will be randomly assigned to one of the two treatment arms (1:1) and receives a unique randomization number. The randomisation will be done and documented centrally and send by fax. Stratification will be performed prior to randomization by Eastern Cooperative Oncology Group Performance Status (ECOG PS) (stratum 1: PS < 2, stratum 2: PS ≥ 2). The randomisation list will be kept in safe and confidential custody at the involved CRO. The method of randomisation and the block sizes themselves will not be disclosed to the study sites, the monitors or any person involved in the clinical trial conduct. This information will be kept with the randomisation list.

### Treatment scheme

After implantation of a catheter patients will be treated as follows:

Both study arms receive a chemotherapy consisting of 2000 mg/m^2^/day 5-FU by IV (24 hours) 200 mg/m^2^/day FA IV (30 min) on day 1, 8, 15 and 22 together with 85 mg/m^2^/day oxaliplatin IV (2 hour) on day 8 and 22. Therapy will be interrupted between days 23 to 42. This cycle will be repeated until any stop-criterion for chemotherapy (disease progression or unacceptable toxicity) is met.

Furthermore, all patients receive nutritional consultation and recommendation by experienced nutritionist contemplated as BSNC.

#### Experimental group

Additionally, patients in experimental group receive a total amount of 1036 ml PN, applied over night via port system. The PN will be administered continuously six days a week. An interruption will be performed during chemotherapy. Beyond, an adjournment of the PN up to two days is possible; an adjournment of three days is only once possible during participation of the clinical trial.

### Evaluation, toxicity-based dose adjustment and follow-up

All patients must have appropriate lab and radiographic studies conducted prior to study enrolment to meet eligibility criteria. Lab parameters will be obtained at least weekly and imaging will be performed every seven weeks. The patient will be asked at each visit for any adverse event (AE) as well as concomitant medication and pain medication. Quality of life (QoL) questionnaires (QLQ-C30 and the pancreas specific PAN 26 questionnaire) will be handed out to all patients on day 1 and day 22 of each cycle prior to chemotherapy. Decisions regarding weekly chemotherapy treatment and chemotherapy dose-adjustment will be made using the guidelines below and based on haematological parameters monitored once weekly during chemotherapy. In case of grade 3 or grade 4 haematological toxicities chemotherapy should be held until resolution or until toxicity has resolved or dropped to grade 2. PN will be continued. The procedures for patients with leukocytes between 1.0/l and 1.5/l will be discussed individually in the study group. In case of grade 3 or grade 4 gastrointestinal toxicities (including anorexia, dehydration, nausea/vomiting, diarrhoea, mucositis and bleeding) patients will be considered for periodic outpatient intravenous rehydration with anti-emetics according to conventional practice guidelines. Any grade ≥ 2 neurotoxicity should lead to discontinuation of chemotherapy until recovery to at least grade 1. All uncertain cases of toxicities will be discussed by the study group discretion.

Patients can withdraw from study participation at any time. Patients are taken off the study if unacceptable toxicity appears. Unacceptable toxicity is defined as serious side effect or irreversible grade 4 toxicity, independent whether they are expected or unexpected. After the individual ending of the study subjects will receive the best available medical and nutritional care. Patients will undergo imaging and lab analysis (including tumor marker) quarterly and will be tracked by quarterly phone follow-up until death.

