#### Sample size estimation

The sample size is calculated to detect differences in the 4-month EFS-rates and is based on a comparison of two groups using the unstratified log rank test. The 4-month EFS-rates are assumed to be 60% and 40% (HR = 0.557) in the experimental and control group, respectively based on data from literature [6,7]. Applying one interim analysis according to group sequential design with two stages using the O'Brien and Fleming type, a 1:1 randomization, and assuming an accrual time of 36 and a follow-up time of 4 months a total of 102 patients and of 93 events are required for a two-sided log rank test with an overall two-sided significance level of 0.05 and power of 0.80 With the expectation that approximately 15% of patients may be lost to follow up, it is estimated that 120 patients will need to be enrolled. Formula of Schoenfeld [14] used for the calculation of the number of events. The ADDPLAN, Version 4.0 calculator was used for the sample size estimation. Stratification of heterogeneous patients regarding performance status prior to randomization may improve the power of the trial. We expect an additional stratification effect and in case of a smaller than the assumed true treatment effect the lost of power will be decreased. The primary analysis will be therefore performed with the stratified log rank test.

The statistical analysis will be carried out by the responsible biostatistician at the National Center for Tumor diseases (NCT) Heidelberg. The analysis will be done as soon as the database has been declared to be complete and accurate and has been locked. The details of the analysis will be laid out in the statistical analysis plan, which will be finalized and approved prior to the database lock. It has to be authorized before by the biometrician, the sponsor, and the Coordinating Investigator.

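### EFS exits without a stopping criterion are censored whatever the reason and QLQ-C30 is not named after them, so unequal, decline-related exits can bias the primary test in either direction

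*Protocol article*

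**What the plan says.** Study objectives gives EFS three components: a QLQ-C30 functional shift of ten points or more, "withdrawal due to fulfilling the special defined stopping criteria for chemotherapy as well as PN and Best Supportive Nutritional Care (BSNC) in Arm A" (with the matching rule for Arm B), "or death from any cause (whichever occurs first". The chemotherapy criteria are progression and unacceptable toxicity. The nutritional criteria are two of three signs (weight or intake, bioimpedance, PINI) and are the same in both arms.

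Evaluation, toxicity-based dose adjustment and follow-up adds that "Patients can withdraw from study participation at any time". It schedules QLQ-C30 on two days of each chemotherapy cycle. After a patient's study ends it names quarterly imaging, laboratory tests and telephone contact for life, but no questionnaire.

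Secondary analyses sets the censoring rule: "For subjects with incomplete follow-up, time to last follow-up date will be used as the censoring time". It also gives the only stated sensitivity analysis of EFS: "A sensitivity analysis will be performed on the primary variable to assess the impact of protocol deviations using the per protocol analysis set".

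Sample size estimation expects that "approximately 15% of patients may be lost to follow up", with no split by arm. Experimental group limits pauses in parenteral nutrition (PN): "an adjournment of three days is only once possible during participation of the clinical trial". It does not say how exceeding that limit is scored.

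**The concern.** A log-rank test treats a censored patient as having the same future risk as those who remain in the same arm. In advanced pancreatic cancer, leaving without a formal criterion is often part of the decline that EFS is meant to capture. Such a patient is removed from the risk set without an event.

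The quality-of-life component then stops being observed, because the forms follow chemotherapy cycles. Progression found later on quarterly imaging is not listed as an event by itself; the listed event is withdrawal for it. Of the three components, only death remains clearly observable.

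If exits of this kind are more frequent in one arm, that arm gains apparent EFS. The trial is open label and the burden of treatment differs by arm, so unequal exits are plausible. The per protocol set needs one completed cycle and at least two post-baseline assessments. It therefore removes early leavers and does not test the assumption made about them.

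**Working it through.** **The plan's own figures first** (inputs from Sample size estimation and Interim analysis).
- HR = ln 0.6 / ln 0.4 = 0.5575.
- Schoenfeld events = 4(1.960 + 0.842)² / (ln 0.5575)² = 91.96. The two-look O'Brien-Fleming inflation of 1.0078 gives 92.67, so 93.
- Event probabilities with 36 months' accrual and 4 months' follow-up are 0.952 (control) and 0.871 (PN), mean 0.911. 93 / 0.911 = 102.1, stated as 102.
- 102 / 0.85 = 120.
- O'Brien-Fleming one-sided levels are 0.0026 and 0.0240.

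All of these reproduce. The expected loss is 0.15 × 120 = 18 patients, against 93 events.

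**Closed-form check with no true effect.** Take 60 patients per arm and the control hazard −ln(0.4)/4 = 0.2291 per month in both arms. If a share q leaves just before its own event and is censored, the observed hazard is (1 − q) times the true one.
- Events: 120 × 0.952 × 0.85 ≈ 97.
- Exits 20% PN / 10% control (12 and 6 patients): HR = 0.80/0.90 = 0.889. Shift = ln(0.889) × √(97/4) = −0.118 × 4.924 = −0.580. At the final critical value 1.977, Φ(−1.977 + 0.580) = 0.081.
- Exits 25% / 5% (15 and 3 patients): HR = 0.75/0.95 = 0.789. Shift = −1.164. Φ(−0.813) = 0.208.

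Simulation at the one-sided 0.024 level (20,000 trials per scenario) gives 0.081 and 0.207. If only half of the exits fall at the event and the rest at a uniform earlier time, it gives 0.066 and 0.140.

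**Does telephone follow-up to death cure it?** A second simulation used exits at 90% of the patient's own event time, a single look at |z| > 1.96 and 20,000 runs. Its death hazard is ln 2 / 5 = 0.139 per month, from the 5-month median survival in Background. Entries are false PN win / false control win / apparent HR.

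| Exits PN/control | Leaver censored at exit | Later death counted |
|---|---|---|
| 15/15 | 0.026 / 0.027 / 0.999 | 0.028 / 0.024 / 0.995 |
| 20/10 | 0.080 / 0.007 / 0.895 | 0.049 / 0.013 / 0.946 |
| 25/5 | 0.181 / 0.001 / 0.805 | 0.087 / 0.007 / 0.893 |
| 10/20 | 0.007 / 0.080 / 1.117 | 0.013 / 0.047 / 1.057 |

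The right-hand column depends on the death model. If survival after exit is instead drawn afresh with a 5-month median, two runs give 0.086 and 0.097 at 20/10, and 0.267 and 0.269 at 25/5. Leavers are then carried as event-free while decline goes unseen. Counting deaths therefore does not reliably remove the bias.

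**Unequal but uninformative exits.** Exits unrelated to the patient's own event time give a false PN win of 0.025 at both 20/10 and 25/5.

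**Counting exits as events.** Where exits fall at the event, the false PN-win rate returns to 0.025 (20/10) and 0.024 (25/5). Where half fall earlier, it drops to 0.018 and 0.011, so the analysis overcorrects against the arm with more exits.

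**The case against.** **PN-only exits.** A reader might infer that some exits exist only in the PN arm, and that a PN benefit could arise simply from who leaves. The documents do not support that. No section says that refusing PN or exceeding the pause limit ends participation. Study objectives makes chemotherapy independent of whether the nutritional intervention continues, so a patient who stops only PN stays on chemotherapy with QLQ-C30 and remains in the ITT set. More exits under nightly infusion are a plausible inference, no more. Control patients may equally leave because they were not given PN, which would bias against it. This objection stands in full.

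**Not every other exit is simply censored.** Death after exit can be recorded by telephone, and some patients who decline will already have had a quality-of-life, progression, toxicity or nutritional event. This stands as a limit on size. It does not remove the problem, as the table shows.

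**Existing safeguards.** It would be too strong to say that nothing in the plan could reveal the problem. Secondary analyses already tabulates disposition and reasons for deviating from therapy, and overall survival is tested. These could show an imbalance in exits but would not show what it does to EFS. The interval-censored alternative in Primary analysis deals with delayed recording of events, not with exits linked to prognosis.

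**Leave it to the SAP.** For the sensitivity analyses alone this is fair, and a full protocol may say more than the article. But the event definition, the questionnaire schedule and the censoring rule are all stated here. Sample size estimation has the SAP finalised only before database lock, when uncollected questionnaires cannot be recovered.

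**Conclusion.** The concern holds in limited form. As stated, the EFS definition, the cycle-bound questionnaires and a censoring rule blind to reason leave the quality-of-life component unobserved in patients who leave or stop chemotherapy without a stopping criterion. If those exits are related to decline and unequal between arms, the primary test is biased towards the arm with more exits, whichever that is.

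At a 20%/10% split the false-win rate for that arm is roughly 0.05 to 0.10 against 0.024. A 25%/5% split gives more, from 0.087 to 0.269 depending on how death after exit is modelled. Equal or uninformative exits leave it near 0.025.

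Only the 15% total comes from the plan. The split, the timing, treating all of that loss as informative, exponential hazards and a single unstratified test are assumptions. The figures show what could happen, not what is expected. The point merits a change to the plan but does not call for a different primary test.

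**What to change.** Keep the stratified log-rank test on the ITT set as primary.

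1. In Evaluation, toxicity-based dose adjustment and follow-up, state that patients who stop chemotherapy or leave treatment without an EFS event continue QLQ-C30 and EFS follow-up, for example at the existing follow-up contacts, unless they withdraw consent to data collection.
2. In Secondary analyses, set the EFS censoring date for patients without an event at the last assessment at which all EFS components were evaluated, not the last telephone contact. Say how a later death known only from telephone contact is scored.
3. Add a sensitivity analysis of EFS that counts exits not due to a stopping criterion as events at the exit date in both arms, read as a bound because it can overcorrect. Add a tipping-point analysis applied to each arm in turn. Split the planned disposition table by arm and reason.

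The second change alone does not remove informative censoring; it only stops unobserved time from being credited as event-free. The first change supplies the missing data, so it has to be in place while patients are still being followed.

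The cost is some wording, a few extra questionnaires from patients off treatment, and re-runs of the planned test. The sensitivity result may be less favourable than the primary one.
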